### Randomization and allocation of interventions

2.5

A computer-generated permuted block randomization sequence, stratified by center, will be used for the randomization process. A web-based platform (www.clipnasis.com) will be used to allocate patients to the interventions. This platform will randomly assign a number to each patient and to the corresponding intervention. Researchers will be blinded to the allocation sequence of the study interventions.

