#### Sample size estimation

2.9.1

One of the participating centers used historical data from the hospital database to calculate the mean time from admission to surgical intervention in patients not receiving antiplatelet treatment and without any coagulopathies: 2.85 days (standard deviation [SD], 3.17). Accepting an alpha risk of 0.05 and a beta risk under 0.20 in a 2-sided contrast and a 10% loss rate, the estimated sample size needed to detect a decrease of ≥1.5 days from admission to surgery was 156 patients (78 subjects in the experimental and control groups, respectively). This calculation was made using v. 7.10 (June 2010) of the GRANMO calculator (available at: https://www.imim.es/ofertadeserveis/en_granmo.html).

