#### Data analysis

2.9.2

The main analysis of efficacy will be made “per protocol”, but an analysis on an Intention-To Treat (ITT) basis will be done to test the consistency of the results. In the “per protocol” analysis will be included patients that have received the corresponding test for platelet function and have been undergoing surgery. In the ITT, analysis will be included all patients randomized independently if they have received the test or the surgery.

The 2 groups will be compared to ensure that there are no significant differences in the clinical variables of interest. Student's *t* test will be applied to check for between-group differences in the main study endpoint (mean time from admission to surgery). The specific statistical analysis of the baseline characteristics will depend on the nature of the evaluated variables. For categorical variables, we will use the chi-square test with the corresponding contingency table. Ordinal or quantitative variables with clear non-normal distribution will be analyzed using the nonparametric test for more than 2 groups (Kruskall-Wallis), including medians with ranges for each group. The *t* test will be used to assess quantitative variables that meet normality criteria, with mean values and SD provided for each group.

All variables showing statistically significant or clinically relevant differences between the groups on the initial comparison will be entered into a multivariate model to confirm that the differences relative to the study's main endpoint remain significant on an analysis of covariance.

The EQ-5D-5L measures 5 dimensions (mobility, self-care, usual activities, pain/discomfort, and anxiety/depression) related to quality of life. Each dimension has 5 levels of severity (no problems, slight problems, moderate problems, severe problems, and extreme problems) which are scored from 1 (no problems) to 5 (extreme problems) points, with the maximum score of 1 indicating a state of full health. The partial results on each dimension and the overall score will be calculated using the scoring algorithms developed by Ramos-Goñi et al.^[24]^ Because this questionnaire yields ordinal data, nonparametric tests will be used to analyze the comparisons. Between-group differences will be analyzed using the Mann-Whitney and Kruskal-Wallis tests.

The EQ-VAS evaluates patient-perceived health status. This is a vertical scale ranging from 0 to 100. An ANalysis Of VAriance (ANOVA) will be performed.

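### The confirmatory model for time to surgery takes its covariates from observed baseline imbalance, so centre is almost never adjusted for and antiplatelet drug only by chance

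*Protocol article*

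**What the plan says.** Section 2.9.2 (Data analysis) of the protocol article sets out three steps.

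- **Balance check.** "The 2 groups will be compared to ensure that there are no significant differences in the clinical variables of interest". The tests for this are then listed by type of variable.
- **Primary test.** Student's t "test will be applied to check for between-group differences in the main study endpoint". No covariate or stratum is attached to it.
- **Confirmation.** "All variables showing statistically significant or clinically relevant differences between the groups on the initial comparison will be entered into a multivariate model". The stated purpose is to see whether the primary difference is still significant after adjustment by analysis of covariance.

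No covariate is named in advance. Two facts elsewhere bear on this.

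- Section 2.5 (Randomization and allocation of interventions): "A computer-generated permuted block randomization sequence, stratified by center, will be used for the randomization process".
- Sections 2.1 (Study design) and 2.8.2 (Control intervention): control patients wait for a time set by their antiplatelet drug, 3, 5, 7 or 10 days. Under section 2.8.1 the same drug-specific time applies in the experimental arm only when platelet function has not normalised after 3 days.

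Neither centre nor drug appears in any analysis of the primary endpoint that the article describes.

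**The concern.** With sound randomisation, baseline differences between arms are due to chance. Testing them cannot ensure balance, and using the results to build a model selects covariates by how they happened to fall rather than by how well they predict time to surgery. The route through clinical relevance is also judged on the observed imbalance. It has no threshold, and the article does not say who judges it, in a trial where researchers know the allocation.

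The rule also tends to miss the covariates that the design points to. Stratification balances centre, so an imbalance rule would almost never select it. Drug is a true baseline variable, since eligibility depends on it, but it enters only if its mix happens to differ between arms.

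At stake are three things: a confirmatory model that nobody can write down before the data are seen, no stated conclusion if the t test and the adjusted model disagree, and precision given away.

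**Working it through.** **1. The plan's own figure.** Section 2.9.1 gives "Accepting an alpha risk of 0.05 and a beta risk under 0.20 in a 2-sided contrast and a 10% loss rate", SD 3.17 days and a difference of 1.5 days.

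n per arm = 2(1.960 + 0.842)² × 3.17² / 1.5² = 70.1, and 70.1 / 0.90 = 77.9. That gives 78 per arm and 156 in total, as stated. The calculation is for an unadjusted comparison. About 70 per arm remain evaluable (78 × 0.90 = 70.2).

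**2. Ignoring the stratum.** Let centre explain a share ρ of the variance. The documents give no value, so 10% and 20% are assumed. With arms balanced within centre:

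- SE used by the t test: 3.17 × √(2/70) = 0.536
- True SE: 0.536 × √(1 − ρ) = 0.508 (ρ = 0.1) or 0.479 (ρ = 0.2)
- True type I error: 2[1 − Φ(1.96/√(1 − ρ))]
- Power, unadjusted: Φ[(1.5 − 1.96 × 0.536) / true SE]
- Power, adjusted: Φ[1.5 / true SE − 1.96]

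| ρ (assumed) | True type I error, unadjusted | Power, unadjusted | Power, centre in model |
|---|---|---|---|
| 10% | 3.9% | 81% | 84% |
| 20% | 2.8% | 83% | 88% |

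**3. The selection rule itself.** This was simulated with 70 per arm, ten baseline variables of which one is prognostic, selection at p < 0.05, and 6,000 runs per setting. The prognostic variable is not balanced by stratification and acts equally in both arms.

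| R² of the prognostic variable (assumed) | Type I, t test and selected model both significant | Power, both significant | Type I, variable always in model | Power, variable always in model |
|---|---|---|---|---|
| 0.1 | 4.3% | 77% | 4.8% | 82% |
| 0.3 | 3.5% | 78% | 4.9% | 91% |
| 0.5 | 3.3% | 78% | 4.8% | 98% |

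The same runs show what happens if an analyst could claim success on either result. The error is then P(t test) + P(selected model) − P(both): 5.15 + 4.75 − 4.28 = 5.6%, 4.78 + 3.95 − 3.53 = 5.2%, and 5.10 + 3.65 − 3.27 = 5.5%. Simulation error is about √(0.05 × 0.95/6000) = 0.3 points. The unbounded choice that clinical relevance allows was not modelled.

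**4. How often chance selects something.** With k independent variables tested at 5%, P(at least one significant) = 1 − 0.95^k, which is 23%, 40%, 54% and 64% for k = 5, 10, 15 and 20. The article does not list the variables, so k is assumed. This shows how readily the rule fires; it does not measure harm.

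**5. Spread from the drug wait.** The article gives no drug mix. For assumed shares on waits of 3/5/7/10 days:

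- 60/40/0/0%: mean 3.8 days, variance 0.6 × 0.8² + 0.4 × 1.2² = 0.96, SD 1.0, and 0.96/3.17² = 10%
- 70/25/3/2%: SD 1.4, 19%
- 50/40/5/5%: SD 1.7, 30%

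The percentages are scheduled control-arm variance set against the planning variance, which comes from patients not on antiplatelets. They are a rough yardstick, not an R² for the trial.

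**The case against.** The strongest reply is that the primary comparison is the t test, which does not depend on any selected covariate; only the confirmatory step does. Requiring both results to be significant cannot raise the type I error above that of the t test. Both points stand. A reader might infer that the error rate is uncontrolled. The documents do not support that: as written, the procedure errs on the conservative side, and nothing in the text permits choosing the more favourable result. What remains is that the article does not say what follows if the two disagree.

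A reader might also infer that significance alone decides selection. It does not: a drug imbalance judged clinically relevant could enter without reaching significance. That softens the point about drug but moves the weight onto an undefined judgement.

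It can be said that unadjusted power of 81% to 83% still exceeds the planned 80%, and that articles often leave stratum terms to the analysis plan. The first is true, and the loss for centre is modest. On the second, the absence of centre alone would be weak. The finding rests on a selection rule that the article states.

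Nor do the documents show that drug is the strongest predictor, or that it fixes the control outcome. They rank no predictors, and the SD of 3.17 days arose in patients with no antiplatelet wait at all.

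**Conclusion.** The concern holds in a limited form. Section 2.9.2 states a poor rule: covariates for the confirmatory analysis are chosen from observed imbalance, which under randomisation is chance. The rule leaves centre out almost always and brings drug in only by accident. The consequences are a model unknown until the data are seen, latitude over which result to stress, and lost precision.

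For centre, the loss is 3 to 5 points of power with a type I error of 3.9% to 2.8%, if centre explains 10% to 20% of the variance. For a strongly prognostic covariate left to the rule the loss is larger, from 5 points at R² 0.1 to 20 points at R² 0.5 in the simulation. That simulation assumes an equal effect in both arms, so it cannot be read directly as the gain from adjusting for drug. All variance shares and drug mixes are assumed. The trial is not invalidated; the change should be made because it is nearly free.

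**What to change.** - Remove baseline significance testing and selection by imbalance. Report baseline characteristics descriptively.
- Pre-specify the primary model as an analysis of covariance with allocation, centre and antiplatelet drug wait class, the last taken from the drug recorded at admission. Fix the rule for pooling small centres and the mapping from drug to wait class before the final analysis.
- Consider a drug-by-arm term, because the wait acts mainly in the control arm. If it is included, centre the drug terms at the pooled drug mix so that the allocation effect remains the average difference.
- Keep the unadjusted t test as a sensitivity analysis, and state that the pre-specified model decides the primary conclusion.

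The cost is a short dated amendment, since the rule stands in the published protocol, and a few degrees of freedom. No new patients or data are needed: centre is known from stratification and drug from eligibility. With 81 of 156 patients included when the article was written, the amendment should rest on the design and be made without sight of outcomes by arm.

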#### Secondary outcomes

2.4.2

Clinical: postoperative bleeding, complications associated with the surgical procedure and surgical wound, medical complications during admission, perioperative mortality and mortality at 1 year, quality of life (EQ-5D-5L generic questionnaire) assessed preoperatively and postoperatively at days 5 and 30 and months 6 and 12.

Costs: length of hospital stay, surgery-associated direct health costs, laboratory tests, medications, consumables, complementary diagnostic tests, resources required to treat perioperative complications, cost associated with rehabilitation, consultations with specialists, and primary care visits after hospital discharge and during follow-up.

A subgroup analysis of 20 consecutive patients from one of the participating centers will be performed to determine the correlation between 2 platelet function systems (PlaTeLet work [PTLwork] versus the conventional Platelet Function Assay [PFA-100 system]).

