For the economic analysis, we will calculate the costs in Euros (€) based on the prices of the local health system. For the cost-effectiveness analysis, the costs of the study intervention will be compared to the incremental results, measured in natural units. Cost-effectiveness will be measured by the time from hospital admission to first mobilization after surgery. If the results in the 2 groups are similar, we will perform a cost minimization analysis. Data will be converted into a unit-cost evaluation to determine average cost per patient. We will conduct a comparative economic evaluation of the 2 study alternatives. Confidence intervals will be used to determine the presence of significant differences.

To perform the cost-utility analysis, we will assess Quality-Adjusted Life Years (QALYs)—measured with the EQ-5D-5L—and cost per QALY, calculated incrementally (Δ cost/Δ QALYs) in each group.

We will perform a deterministic sensitivity analysis to evaluate the robustness of the results. The level of significance for all statistical analyses will be set at 5%. The SPSS statistical software program (v. 24) will be used to perform the statistical analyses.

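### The cost-effectiveness analysis switches to cost minimisation on an undefined similarity, and the EQ-5D-5L index is compared by rank tests that give no mean difference and use no baseline

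*Protocol article*

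**What the plan says.** All of this is in the protocol article.

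- **Economic rule (section 2.9.2).** The effect in the cost-effectiveness analysis is time from admission to first mobilisation. The rule that follows is "If the results in the 2 groups are similar, we will perform a cost minimization analysis". Neither the results meant nor the degree of similarity is defined. A later sentence in the same paragraph says that confidence intervals will show whether differences are significant.
- **Cost-utility (section 2.9.2).** A separate paragraph plans QALYs from the EQ-5D-5L and a cost per QALY, "calculated incrementally (Δ cost/Δ QALYs) in each group". It is not made conditional on the rule above. The only sensitivity analysis named is deterministic.
- **EQ-5D-5L comparison (section 2.9.2).** Dimension results and an overall score, with 1 as full health, are derived by a published algorithm. The reason given for the choice of test is "Because this questionnaire yields ordinal data, nonparametric tests will be used to analyze the comparisons", and Mann-Whitney and Kruskal-Wallis are named. The EQ-VAS is to be analysed by ANOVA, with no factors stated.
- **Timing (section 2.4.2).** The plan has "quality of life (EQ-5D-5L generic questionnaire) assessed preoperatively and postoperatively at days 5 and 30", and again at months 6 and 12.
- **Covariate adjustment (section 2.9.2).** The only analysis of covariance described concerns the main endpoint.

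**The concern.** A cost-minimisation analysis is justified when effects are known to be equivalent. Here the decision to make that assumption is taken from the trial's own results, with no margin, in a trial sized for a different outcome (time to surgery). If the trigger fires wrongly, effects leave the comparison and the cheaper strategy wins by default. Cost-effectiveness is a stated secondary objective (section 2.2.2), so this conclusion will be read.

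The EQ-5D-5L rationale is also inconsistent with the plan's own use of the instrument. The five dimension levels are ordinal. The index from a value set is a utility, and computing QALYs from it treats it as a cardinal quantity. A rank test on the index does not estimate the mean difference that readers of the QALY analysis will want beside it. A preoperative value is collected, yet no named analysis is stated to use it.

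**Working it through.** **Step 1. Reproduce the plan's sample size.** Inputs from section 2.9.1: "Accepting an alpha risk of 0.05 and a beta risk under 0.20 in a 2-sided contrast and a 10% loss rate"; mean and spread "2.85 days (standard deviation [SD], 3.17"; target "decrease of ≥1.5 days from admission to surgery was 156 patients".

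- n per group = 2 × [SD × (1.960 + 0.842) / difference]² = 2 × [3.17 × 2.802 / 1.5]² = 70.11.
- With 10% loss: 70.11 / 0.90 = 77.9, so 78 per group and 156 in total. The stated figure is reproduced.
- Evaluable per group after the planned loss: 78 × 0.90 ≈ 70.

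The calculation concerns time to surgery only. No size, SD or margin is given for time to mobilisation, EQ-5D-5L, QALYs or cost.

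**Step 2. How often would a real difference look similar?** Assumption: similar means not significant at 5%, two-sided, by a normal-approximation comparison of means. Differences are in SD units because no SD is given for time to mobilisation.

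- Standard error = √(2/70) = 0.169 SD.
- 95% CI half-width = 1.96 × 0.169 = 0.33 SD.
- P(not significant) = Φ(1.96 − d/0.169) − Φ(−1.96 − d/0.169).

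| True difference d (SD) | d / 0.169 | P(judged similar) |
|---|---|---|
| 0.2 | 1.18 | 0.78 |
| 0.3 | 1.77 | 0.57 |
| 0.4 | 2.37 | 0.34 |
| 0.5 | 2.96 | 0.16 |

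Even an observed difference of exactly zero would leave true differences of up to about a third of an SD, in either direction, inside the interval.

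**Step 3. What does leaving out the baseline cost?** The correlation r between preoperative and follow-up values is not in the document, so a range is assumed. The comparison is between a baseline-adjusted and an unadjusted difference in means. It is not a comparison with the planned rank test.

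- Residual variance factor = 1 − r².
- Equivalent increase in patients = 1 / (1 − r²).
- Power for a 0.3 SD difference at 70 per arm = Φ(0.3 / [0.169 × √(1 − r²)] − 1.96). Without adjustment it is 0.43.

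| Assumed r | 1 − r² | Variance removed | Patient multiplier | Power for 0.3 SD |
|---|---|---|---|---|
| 0.3 | 0.91 | 9% | 1.10 | 0.46 |
| 0.5 | 0.75 | 25% | 1.33 | 0.54 |
| 0.7 | 0.51 | 49% | 1.96 | 0.70 |

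**Step 4. Chance imbalance.** With an assumed utility SD of 0.25 and 78 per arm, a baseline imbalance of one standard error shifts an unadjusted utility difference by r × 0.25 × √(2/78) = r × 0.040. That is 0.012, 0.020 or 0.028 for r = 0.3, 0.5 or 0.7.

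**The case against.** Several points on the other side are sound, and they limit the concern.

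- **The switch does not remove the QALY analysis.** The rule follows the mobilisation measure, and the cost-utility analysis is planned regardless. A reader might infer that QALYs are discarded when groups look alike. The text does not say so.
- **Rank tests do not corrupt the cost per QALY.** They compare EQ-5D-5L scores, and no rank statistic enters the QALY calculation. Under randomisation an unadjusted rank test is valid. The loss is precision, uncorrected chance imbalance and the absence of a mean difference, not systematic error.
- **Similar is undefined.** Equating it with non-significance draws on the nearby sentence about confidence intervals, which is not stated as the trigger. This stands, but it does not rescue the rule: similarity judged by eye would be data-dependent too, with no error rate at all.
- **Rank tests suit part of the instrument.** They are reasonable for the dimension levels, which are also to be reported.
- **Silence is not exclusion.** The EQ-VAS ANOVA could be a repeated-measures model that includes the preoperative assessment. Baseline adjustment of QALYs may be in the full plan.
- **Deaths.** A reader might apply the 18–33% first-year mortality in the Introduction to 156 patients and infer that 28 to 51 are dropped at month 12 (0.18 × 156; 0.33 × 156). No rule restricting the comparison to survivors is stated, so this is not supported.
- **The ratio in each group.** One might read this as a different estimand. The formula given is incremental, and the section promises a comparison of the two alternatives, so it is loose wording.

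**Conclusion.** The concern holds in two limited parts.

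First, the cost-minimisation trigger is badly fixed. It has no margin, and the trial cannot show equivalence by non-significance: the 95% CI half-width is about 0.33 SD at 70 per arm, and true differences of 0.2 to 0.4 SD would pass as similar in about 78% to 34% of trials. Those percentages rest on reading similar as non-significant and on the 10% loss in section 2.9.1. What is directly at risk is the cost-effectiveness conclusion on time to mobilisation.

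Second, the ordinal rationale does not fit the index, and the named rank tests neither estimate a mean utility difference nor, as stated, use the collected preoperative value. The 9% to 49% of variance forgone depends entirely on the assumed correlation. The preoperative value is taken after the fracture, so its correlation with later utility is uncertain.

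The document does not support saying that the QALY result will be wrong. These are secondary analyses, and the primary endpoint is unaffected.

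**What to change.** - Delete the cost-minimisation switch. Always report between-arm incremental cost and incremental effect, both for time to mobilisation and for QALYs, with bootstrap confidence intervals.
- Analyse the EQ-5D-5L index and the EQ-VAS by ANCOVA or a repeated-measures model, adjusted for the preoperative value and centre, and report the mean difference with its interval. Adjust the QALY difference for baseline utility.
- State that the preoperative value is taken at admission, before the arms diverge. The control arm waits longer by design, so a value taken shortly before surgery could already reflect the allocated strategy and should not serve as a covariate.
- Keep rank tests for the five dimension levels, where the ordinal argument applies.

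The cost is a change of wording and modest programming. No extra patients or assessments are needed if the preoperative questionnaire is already completed at admission. The economic conclusion may have to be stated with wider uncertainty than a cost-minimisation result would show.

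### The cost-effectiveness analysis switches to cost minimization if the arms look 'similar', with no equivalence margin, in a trial too small to show that time to mobilization is equal

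*Protocol article*

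**What the plan says.** The economic part of section 2.9.2 (Data analysis) of the protocol article sets out two analyses.

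- **Cost-effectiveness.** Costs are set against incremental results in natural units: "Cost-effectiveness will be measured by the time from hospital admission to first mobilization after surgery". The next sentence is the rule at issue: "If the results in the 2 groups are similar, we will perform a cost minimization analysis". After describing average cost per patient and a comparative evaluation of the two strategies, the paragraph ends: "Confidence intervals will be used to determine the presence of significant differences".
- **Cost-utility.** A separate paragraph plans QALYs from the EQ-5D-5L and "cost per QALY, calculated incrementally (Δ cost/Δ QALYs) in each group". It states no condition.

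For robustness the section says: "We will perform a deterministic sensitivity analysis to evaluate the robustness of the results". A 5% significance level applies to all analyses. Nothing in the article says how close two results must be to count as similar.

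Section 2.9.1 (Sample size estimation) sizes the trial to detect a reduction of at least 1.5 days in time from admission to surgery. It does not address mobilization or costs.

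**The concern.** Cost minimization compares costs alone. That is sound only when the effects are known, or have been shown, to be equal within a margin that does not matter. Here the choice of method depends on the observed effect, and similarity is undefined. If the analyst falls back on the criterion the paragraph does offer, an interval that includes zero will count as similar. In a trial of this size such an interval can also include differences worth having.

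The economic conclusion can then turn on imprecision. Suppose platelet-function testing costs somewhat more and brings mobilization forward by an amount the trial cannot separate from zero. Cost minimization would favour the control strategy. Suppose instead that testing costs less and mobilization is somewhat later. Cost minimization would favour testing and give the delay no weight. In both cases the economic comparison treats an imprecise effect difference as exactly zero. A deterministic sensitivity analysis does not repair this: it varies inputs such as unit costs and does not carry the joint sampling uncertainty of cost and effect.

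Cost-effectiveness is a named secondary objective, and the Discussion opens by presenting it, with efficacy, as what the trial will assess.

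**Working it through.** **Inputs from the document (section 2.9.1).** SD 3.17 days for time from admission to surgery; target difference 1.5 days; 78 per arm, 156 in total; "Accepting an alpha risk of 0.05 and a beta risk under 0.20 in a 2-sided contrast and a 10% loss rate".

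**Assumptions.** The document gives no SD for time to first mobilization, so 3.17 days is borrowed and then varied from 2 to 6 days. The true differences of 0.5, 1.0 and 1.5 days are illustrative; 1.5 days is the design effect for time to surgery.

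**Step 1: the plan's own sample size.** Per arm, n = 2 × [SD × (1.960 + 0.842) / difference]² = 2 × [3.17 × 2.802 / 1.5]² = 70.1. Allowing for 10% loss, 70.1 / 0.9 = 77.9, so 78 per arm and 156 in total. The stated figure reproduces, and it implies about 70 evaluable patients per arm.

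**Step 2: precision for mobilization.** SE = SD × √(2/70) = 3.17 × 0.169 = 0.536 day. The 95% half-width is 1.96 × 0.536 = 1.05 days, about 25 hours.

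**Step 3: chance that a real difference d is non-significant** (normal approximation, two-sided 5%). P = 1 − [Φ(d/SE − 1.96) + Φ(−d/SE − 1.96)]. For d = 1.0 and SD 3.17, d/SE = 1.866 and P = 0.537.

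| SD (days) | 95% half-width (days) | d = 0.5 day | d = 1.0 day | d = 1.5 days |
|---|---|---|---|---|
| 2.00 | 0.66 | 0.684 | 0.159 | 0.007 |
| 3.17 | 1.05 | 0.846 | 0.537 | 0.201 |
| 4.50 | 1.49 | 0.899 | 0.740 | 0.495 |
| 6.00 | 1.99 | 0.922 | 0.833 | 0.684 |

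**Step 4: what a positive claim of similarity would need.** Take two one-sided tests at 5%, a true difference of zero, SD 3.17 and 80% power. Then n per arm = 2 × [3.17 × (1.645 + 1.282) / margin]². With 70 per arm, power = 2Φ(margin/SE − 1.645) − 1, set to zero if negative. The margins are assumptions.

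| Margin (days) | n per arm (total), before loss | Power with 70 per arm |
|---|---|---|
| 0.5 | 689 (1378) | 0% |
| 1.0 | 173 (346) | 18% |
| 1.5 | 77 (154) | 75% |

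At this SD, of the three margins only the 1.5-day one, as wide as the effect the trial was sized to detect, gives an equivalence claim a reasonable chance of success, and even then power is below 80%.

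**The case against.** Several points on the other side are fair.

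- **Scope.** A reader might infer that the whole economic evaluation switches, so that a QALY gain or loss would also be set aside. The text does not support this. The rule directly follows the mobilization measure, and the cost-utility analysis has its own paragraph with no condition. Incremental cost per QALY is planned either way, so power for QALYs has no bearing on the rule.
- **Meaning of 'similar'.** The article does not equate it with 'non-significant'. The confidence-interval sentence comes after the cost description and may refer to costs. For baseline comparisons the same section also allows clinical relevance as a criterion. The reading used here is therefore an inference. If similarity is instead a matter of judgement once results are seen, the rule is still undefined and still depends on the data.
- **Size.** Time to mobilization contains time to surgery, so the trial is not without information on it. If the gain reaches the 1.5-day design effect, the chance of a non-significant result falls to 20% at SD 3.17. That SD comes from patients not on antiplatelet treatment. It would be wrong to say that the switch misfires in more than half of trials generally.
- **Reporting and error rates.** Nothing says the effect estimate would go unreported. Nor does the rule invalidate the trial's stated error rates: the alpha and beta in section 2.9.1 belong to the primary endpoint, which it does not touch.
- **Condensed article.** Bootstrap methods, acceptability curves and the like are commonly left to a fuller document, and their absence is no fault. A deterministic sensitivity analysis is not an error in itself. The conditional rule, however, is stated in the article, so it can be judged as it stands.

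**Conclusion.** The point holds for the cost-effectiveness analysis on time to first mobilization, and only there. The plan fixes a data-dependent move to cost minimization without an equivalence margin, in a trial sized for superiority on a different, though overlapping, interval. Under the most likely reading of 'similar', and with the borrowed SD, the switch would follow about 85%, 54% or 20% of the time when the true gain is 0.5, 1.0 or 1.5 days. These figures rest on 70 evaluable patients per arm, an SD that the document does not give for this outcome, and chosen true differences. The spread at 1.0 day, from 16% to 83%, shows how far they depend on the SD. That a non-significant result cannot stand for equal effect does not depend on those inputs.

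The consequence is limited to a secondary objective. The primary endpoint, the sample size and the planned cost-utility analysis are unaffected. The change should be made, but the trial's main conclusion does not hang on it.

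**What to change.** Delete the conditional sentence on cost minimization. State that the between-arm differences in cost and in time to first mobilization will always be estimated and reported jointly, whatever their p-values. Give their sampling uncertainty, for example by a non-parametric bootstrap of patients within arm that yields a confidence interval for incremental net benefit. As the document gives no value for a day of earlier mobilization, show net benefit over a range of values. Keep the deterministic sensitivity analysis for unit-cost assumptions.

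Keeping the switch with a pre-specified margin is less attractive, because this sample could rarely meet a margin of 1 day or less at the borrowed SD. Make the change before effect results are compared by arm.

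The cost is a wording change and a few hours of programming on data already collected. The bootstrap may need software beyond the named package. No extra patients, visits or measurements are needed.
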